## Abstract

**Background:**

Science-driven storytelling and entertainment-education (E-E) media demonstrate potential for promoting improved attitudes and behavioral intent towards health-related practices. Months after the outbreak of coronavirus disease 2019 (COVID-19), emerging research highlights the essential role of interventions to improve public confidence in the COVID-19 vaccine. To improve vaccine confidence, we designed three short, animated videos employing three research-informed pedagogical strategies. These can be distributed globally through social media platforms, because of their wordless and culturally accessible design. However, the effectiveness of short, animated storytelling videos, deploying various pedagogic strategies, needs to be explored across different global regions.

**Methods/design:**

The present study is a multi-site, parallel group, randomized controlled trial (RCT) comparing the effectiveness of (i) a storytelling-instructional-humor approach, (ii) a storytelling-analogy approach, (iii) a storytelling-emotion-focused approach, and (iv) no video. For our primary outcomes, we will measure vaccine hesitancy, and for secondary outcomes, we will measure behavioral intent to seek vaccination and hope. Using online platforms, we will recruit 12,000 participants (aged 18–59 years) from the USA and China, respectively, yielding a total sample size of 24,000.

**Discussion:**

This trial uses innovative online technology, reliable randomization algorithms, validated survey instruments, and list experiments to establish the effectiveness of three short, animated videos employing various research-informed pedagogical strategies. Results will be used to scientifically support the broader distribution of these short, animated video as well as informing the design of future videos for rapid, global public health communication.

**Trial registration:**

German Clinical Trials Register DRKS #00023650. Date of registration: 2021/02/09.

**Supplementary Information:**

The online version contains supplementary material available at 10.1186/s13063-022-06067-5.

## Background and rationale

In the midst of the COVID-19 pandemic, research highlights the critical role of interventions to increase vaccine confidence, even before vaccines for COVID-19 become universally available [1, 2]. The WHO has dubbed vaccine hesitancy one of the greatest threats to global health [3], yet we are lacking interventions that effectively promote vaccine confidence in ways that are accessible and globally scalable. Many existing interventions have focused on providing information in the form of scientific data, using a didactic approach. This strategy has proven ineffective for key target audiences [4].

Designing effective interventions for a broad range of target audiences has become even more important during the COVID-19 pandemic as misinformation has spread rapidly around the world. Negative claims about vaccines often appeal to the emotions of the target audiences, eliciting vaccine doubt and hesitancy. This observation—that emotion-focused messages resonate and affect health behaviors [4, 5]—can also potentially be used to the advantage of health communicators. Research suggests that activating positive emotions, like hope and altruism, can actually bolster vaccine education interventions [5].

Other promising pedagogical strategies, including the use of instructional humor [6], analogies [7, 8], and storytelling, could also be leveraged to promote vaccine confidence, and researchers have advocated for a transdisciplinary approach to successful health communication on vaccines [4]. By integrating different fields of expertise, including those outside of academia—like entertainment and marketing—we may be able to design more effective vaccine promotion interventions. Animated E-E videos, developed using transdisciplinary approaches, could be an especially effective method for distributing evidence-based health messages globally through social media platforms [9, 10].

To improve vaccine confidence, we designed three videos, employing three research-informed pedagogical strategies: (i) a storytelling-instructional-humor approach (ii) a storytelling-analogy approach (iii) a storytelling-emotion-focused approach.

The first prototype video was released on Stanford Medicine’s YouTube channel (https://youtu.be/Ut_6GInouYg) on October 19th, 2020, and was viewed 27,290 times within the first 3 weeks. This video belongs to a collection of science-driven, storytelling COVID-19 animations that have already reached several million viewers globally. Because all of the videos contain no spoken words, these interventions can be rapidly distributed to global audiences without translation. Video interventions could play an important role in broadly disseminating health information during the COVID-19 pandemic, but there is a need to evaluate the efficacy of such interventions for improving vaccine confidence.

A secondary aim of the intervention videos is to convey hope, a measurable parameter that research suggests is related to improved health, psychosocial, and academic outcomes [11]. Recent research even suggests that leveraging positive emotions, including hope, may be leveraged as part of COVID-19 vaccine education interventions [5]. Hope has been defined as the perceived capacity to build pathways towards our goals and motivate ourselves to use those pathways. Hope theory proposed by Snyder [11] has been likened to the theories of optimism, self-efficacy, and self-esteem. Especially during the COVID-19 pandemic, a period characterized by widespread emotional distress [12], bolstering hope could have meaningful positive effects on the mental health of the global public.

The aim of this study is to systematically evaluate the efficacy of animated, short video interventions, with different pedagogical approaches, for (a) reducing vaccine hesitancy, (b) increasing behavioral intent to get vaccinated, and (c) increasing hope. Here, we propose an online experiment in which the video intervention and a survey will be randomly ordered and assigned to 24,000 participants between the age of 18 and 59, living in China or the USA. These two countries represent a considerable population in the world, which are culturally different from the other and have also managed the pandemic in significantly different ways [13]. Results will be used to scientifically support the ongoing distribution of these interventions as well as optimizing the design of future animated, E-E videos for public health communication.

## Objective

Our study aims to achieve the following objectives. To:
Establish the effectiveness of each of the intervention videos in reducing COVID-19 vaccine hesitancy (primary objective).Establish the effectiveness of each of the intervention videos in increasing behavioral intent towards COVID-19 vaccination.Establish the effectiveness of each of the intervention videos in increasing participants’ level of hope.

## Methods: participants, interventions, and outcomes

### Study setting

This trial will be conducted online, using the SPIRIT reporting guidelines [14]. For the United States, we will use the research platform created and managed by Prolific Academic Ltd (ProA: https://www.prolific.co/) to recruit participants and an online web platform Gorilla (www.gorilla.sc) to host and deploy our study; for China, we will use Kurundata, which recruits members in a variety of ways, including through its own platform (https://www.kurundata.com/), partnerships with other websites, and encouraging registered members to recruit new members through the popular mobile application WeChat (Appendix S1).

### Trial design

Our study is a multi-site, parallel group, randomized controlled trial (RCT) comparing the effectiveness of each of the short intervention videos with each other and with no video (the control condition). Via the online research platforms, participants will be randomly assigned to four intervention arms (Video A: storytelling-instructional-humor approach, Video B: storytelling-analogy approach, Video C: storytelling-emotion-driven approach) and a control arm (no video). Participants will be randomized at a 1:1:1:1 ratio (Fig. 1). In each trial arm, there is a questionnaire survey, arranged in the following order. *Intervention arm a*: participants will receive the storytelling-instructional-humor video, followed by the survey. *Intervention arm b*: participants will receive the storytelling-analogy video, followed by the survey. *Intervention arm c*: participants will receive the storytelling-emotion-focused video, followed by the survey. *Control arm*: participants will first receive the survey. After survey responses are submitted, participants in the control arm will be given access to the video interventions arranged in a single loop (to ensure post-trial access to treatment).

**Fig. 1 Fig1:**
[figure not shown]
Study design with 24,000 participants randomized to receive the video and questionnaire (treatment arm) or questionnaire and video (control arm)

### Eligibility criteria

To be eligible, participants must be between the age of 18 and 59, living in China or the USA. Since this video is wordless and culturally inclusive, therefore accessible to participants of all language and cultural groups. The English questionnaire will be translated into Chinese, so participants from the USA must have reading competency in English, and participants from China must have reading competency in Chinese to complete the trial questionnaire. Those who do not sign the consent form or drop out will be excluded from the data analysis.

### Ethical approval

Ethics approval was obtained from the Stanford University IRB on January 12th, 2021, protocol #59503, and from the Chinese Academy of Medical Sciences & Peking Union Medical College IRB on March 10th, 2021.

### Who will obtain informed consent?

Participants must preview an information and consent form before they can begin the survey. The form explains the purpose of the study, the risks and benefits of the research, and how to contact the study investigators (or the Stanford University ethics review board). By clicking the link, participants consent to participate in our study and will be redirected to the Gorilla or Kurundata platform, where additional information is given. Participants can exercise their freedom to participate (or decline participation) at recruitment or at any point during the study.

### Criteria for discontinuing or modifying allocated interventions

Since this is a minimal risk study of an online educational video intervention, we do not anticipate needing to discontinue or modify the allocated interventions during the course of the study. Participants can withdraw from the study at any time and participants will not be compensated for incomplete surveys. Those participants who choose not to sign the consent form or fail to complete the experiment in its entirety will be excluded from the data analysis.

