## Interventions

### Intervention description

The video interventions are a short (2–3-min) animated E-E videos about vaccines. All videos use a storytelling approach, but each video differs slightly in its pedagogical approach. *Intervention arm a* will view a video that uses a storytelling-instructional-humor approach. *Intervention arm b* will view a video that uses a storytelling-analogy approach and *intervention arm c* will view a video that uses a storytelling-emotion-focused approach. The videos were developed with input from advisors at the Immunization Action Coalition, Vaccinate Your Family (formerly, Every Child by Two), the Stanford University Pediatrics Dept. Division of Infectious Diseases, the Icahn School of Medicine, the University of Texas Rio Grande Valley School of Medicine, and the Heidelberg Institute of Global Health. The video interventions have no words, speech, or text, but incorporate soundtracks consisting of music and sound effects. The videos demonstrate how COVID-19 has impacted lives around the world and how a vaccine could catalyze a partial return to pre-pandemic lifestyles. The videos are designed for universal reach and optimized for release on social media. The interventions can be viewed at the links below in countries that allow access to YouTube:

Video A: https://youtu.be/ap8xpyREaTc

Video B: https://youtu.be/fYYBJ0d6gl0

Video C: https://youtu.be/WH5KUhGtfa8

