### Assignment of interventions: allocation

All participants who give consent for participation and who fulfill the inclusion criteria will be randomized. After they complete the consent form, Gorilla and Kurundata will use a web-based randomization algorithm to randomly allocate participants to the intervention arm a, intervention arm b, intervention arm c, or control arm (sequence generation) at a 1:1:1:1 ratio. The randomization algorithm involves a web-based algorithm using random permutation, which is independent from the researchers who will recruit patients and implement the protocol. Once an arm of participants is fully recruited, subsequent participants will be randomly assigned to the remaining groups until all arms are fully recruited.

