#### Plans to promote participant retention and completion

Participants will be automatically timed out from the online platform if they take more than 45 min to complete the study. Though participants can withdraw the study at any time, they will not be compensated for incomplete survey participation. Incomplete data will be excluded from our analyses. Since the participants are anonymous to us, there is no way to initiate follow-up in the time limit.

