#### Methods in analysis to handle protocol non-adherence and any statistical methods to handle missing data

Participants who decide to withdraw from the trial will not be replaced

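### The completer-only analysis drops participants after randomisation, and only the video arms must watch a video before the survey, so the video-versus-control contrast can be biased

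*Protocol article*

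**What the plan says.** The exclusion rule appears three times in the protocol article:

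- Eligibility criteria: "Those who do not sign the consent form or drop out will be excluded from the data analysis".
- Criteria for discontinuing or modifying allocated interventions: those who "fail to complete the experiment in its entirety will be excluded from the data analysis".
- Plans to promote participant retention and completion: "Incomplete data will be excluded from our analyses". The same section says that leavers cannot be followed up.

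The section headed for non-adherence and missing data adds only this: "Participants who decide to withdraw from the trial will not be replaced".

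On timing, Assignment of interventions: allocation says: "After they complete the consent form, Gorilla and Kurundata will use a web-based randomization algorithm to randomly allocate participants". Under Trial design, arm a is described thus: "participants will receive the storytelling-instructional-humor video, followed by the survey". Arms b and c follow the same order. The control arm starts with the survey, and then: "After survey responses are submitted, participants in the control arm will be given access to the video interventions arranged in a single loop". Intervention description gives the length: "The video interventions are a short (2–3-min) animated E-E videos about vaccines".

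**The concern.** Refusing consent happens before allocation and does no harm to the comparison. Leaving later is different, because by then the arms are doing different things. A participant in a video arm must watch a pro-vaccine film before reaching the first question, while a control participant reaches it at once. If people who dislike the message leave during the film, the completers left in the video arms are less hesitant than those left in control, even when the film changes nobody's mind.

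The primary contrast is exposed because the planned difference is only 0.01 on a 1–5 score, or 0.1 SD. The standard error shrinks as recruitment grows and the bias does not, so a larger trial makes a false positive more likely.

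The rule can also discard hesitancy scores already given by someone who stops at another part of the survey. How often depends on the order of the items, which the article does not state.

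**Working it through.** **Inputs from the Sample size section:** difference 0.01 (2.00 against 2.01), SD 0.10 (0.12 as sensitivity), α = 0.05, power 80%, 12,000 per country. At 1:1:1:1 allocation, 12,000 / 4 = 3,000 per arm per country.

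**Assumed, because the article gives no figure:** the excess loss in a video arm over control, and the gap in mean hesitancy between leavers and stayers.

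**Step 1: reproduce the plan's figure.** n = 2 × SD² × ((1.960 + 0.842) / 0.01)². At SD 0.10 this gives 1570 per arm, as stated. At SD 0.12 it gives 2261 (stated 2260). The effect size and SD are therefore read as intended.

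**Step 2: bias formula.** Let p be the proportion lost in an arm and g the mean of leavers minus the mean of stayers. The overall mean equals the stayers' mean plus p × g, so the completer mean is too low by p × g. With the same g in both arms, the bias in the contrast is (p_video − p_control) × g.

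**Step 3: effect on the test.** At 3,000 per arm, SE = 0.10 × √(2/3000) = 0.00258. With no true effect and bias b, the two-sided 5% test rejects with probability Φ(b/SE − 1.96) + Φ(−b/SE − 1.96). The SE ignores the small reduction in numbers.

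| Excess loss | Gap | Bias at SD 0.10 | b/SE | Type I error |
|---|---|---|---|---|
| 3% | 1 SD | 0.03 × 0.10 = 0.003 | 1.16 | 21% |
| 5% | 0.5 SD | 0.05 × 0.05 = 0.0025 | 0.97 | 16% |
| 5% | 1 SD | 0.05 × 0.10 = 0.005 | 1.94 | 49% |
| 10% | 1 SD | 0.10 × 0.10 = 0.010 | 3.87 | 97% |

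With the gap in SD units, the last column does not depend on the SD. In the pooled two-country analysis (about 6,000 per arm, SE = 0.10 × √(2/6000) = 0.00183), the second row rises from 16% to about 28%.

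**Step 4: what it takes to reach 0.01.** At SD 0.10 the excess loss must be 0.01 / 0.10 = 10% for a 1 SD gap, or 0.01 / 0.05 = 20% for a 0.5 SD gap. In the extreme case of a normal score where exactly the most hesitant fraction d leaves, the bias is SD × φ(z(1−d)) / (1−d), which equals 0.01 at d of about 4.5%. At SD 0.12 the corresponding figures are 8.3%, 16.7% and 3.7%.

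**The case against.** The strongest reply concerns size and direction. Controls can quit too, since they face the same questionnaire. Consent explains the study's purpose before allocation, so some objectors leave beforehand. Payment requires completion in every arm, and the film is short. No dropout figure by arm exists. All of this stands: loss need not be confined to the video arms, and its direction is plausible rather than known. The comparisons between videos, which are of similar length, do not share the difference in burden.

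A reader might also infer that a false positive is almost certain, by pairing a gap of 0.5 points on the 1–5 scale with the plan's SD of 0.10. The plan's figures do not support that, because such a gap is 5 SD. With a normal score and exactly the most hesitant 3% leaving, the gap is at most 0.234 and the bias at most 0.03 × 0.234 = 0.0070. A 0.8-point gap in 5% of people would need an SD of at least √(0.05 × 0.95 × 0.8²) = 0.174 under any distribution.

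Nor do the documents establish that controls who submit every answer would be dropped for leaving the post-survey videos. Trial design offers access only, as a post-trial benefit, and two of the sections link non-completion to incomplete surveys. The Fig. 1 caption lists questionnaire and video for the control arm, so this is an ambiguity to close.

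Finally, sensitivity analyses are often left to an analysis plan. That does not answer the point, because the completer-only rule is written here three times, and a plan that analysed everyone randomised would contradict it.

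**Conclusion.** The point holds: following the stated rule can bias the primary video-versus-control contrast. Under the assumed 3% to 5% excess loss and gaps of 0.5 to 1 SD, the bias is 0.0025 to 0.005 at the planned SD, and the nominal 5% test rejects in about 16% to 49% of trials with no effect.

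A reader might infer that the bias is likely to exceed the planned 0.01. The article does not show this. It would take about 10% excess loss at a 1 SD gap, or about 4.5% in the extreme case. But a bias well below 0.01 already spoils the test at this sample size. These sizes rest on the assumed loss and gap, on an equal gap in the arms compared, and on the leavers being the more hesitant. If the leavers were less hesitant, the bias would run against the videos.

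**What to change.** - **Analysis set.** Replace the exclusion rule in all three sections. Analyse, by assigned arm, every randomised participant with an available hesitancy score, whether or not other items were completed, as far as the platforms retain partial records and consent allows their use. The article states neither, so both need checking.
- **Completion.** Define control completion as survey submission, so that the videos offered afterwards play no part.
- **Reporting.** Give the number randomised and the number scored, by arm and country.
- **Sensitivity analysis.** Using partial answers does not recover people who quit during the film, since they have no score, no baseline hesitancy measure and no follow-up. For them, add one of two analyses to the video-versus-control contrasts. Trimming bounds remove the excess share from each tail of the better-retained arm in turn, and assume that assignment moves completion in one direction only. A delta-adjusted analysis shifts the missing scores over a stated range.

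This changes analysis and reporting only and needs no new recruitment, so it does not depend on whether data collection has finished. The cost is a little more analysis work and possibly a less favourable stated result.

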## Interventions

### Intervention description

The video interventions are a short (2–3-min) animated E-E videos about vaccines. All videos use a storytelling approach, but each video differs slightly in its pedagogical approach. *Intervention arm a* will view a video that uses a storytelling-instructional-humor approach. *Intervention arm b* will view a video that uses a storytelling-analogy approach and *intervention arm c* will view a video that uses a storytelling-emotion-focused approach. The videos were developed with input from advisors at the Immunization Action Coalition, Vaccinate Your Family (formerly, Every Child by Two), the Stanford University Pediatrics Dept. Division of Infectious Diseases, the Icahn School of Medicine, the University of Texas Rio Grande Valley School of Medicine, and the Heidelberg Institute of Global Health. The video interventions have no words, speech, or text, but incorporate soundtracks consisting of music and sound effects. The videos demonstrate how COVID-19 has impacted lives around the world and how a vaccine could catalyze a partial return to pre-pandemic lifestyles. The videos are designed for universal reach and optimized for release on social media. The interventions can be viewed at the links below in countries that allow access to YouTube:

Video A: https://youtu.be/ap8xpyREaTc

Video B: https://youtu.be/fYYBJ0d6gl0

Video C: https://youtu.be/WH5KUhGtfa8

### Explanation for the choice of comparators

The comparators are similar-length E-E videos, all animated in the same styles by the same animator. They all convey the same message (i.e., vaccines work) using a storytelling approach, without the use of spoken or written language. Each intervention arm video uses a slightly different pedagogical approach. The control arm receives no video intervention. Comparing the *intervention arms a, b* and *c* with the control arm will allow us to quantify the effect of each intervention on the primary and secondary outcomes. Comparing *intervention arms a, b* and *c* with each other will allow us to explore the differential effect of these pedagogical approaches on the primary and secondary outcomes. We will use list experiments, also referred to as the unmatched count technique [15], to eliminate social desirability bias regarding vaccine-seeking behavioral intent. For the list experiments, we will use the control list as the comparator.

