This study is expected to establish the effectiveness of short, animated, E-E videos, using different pedagogical approaches, for improving vaccine confidence. We hope to document a reduction in vaccine hesitancy and guide future E-E video development strategies to support education and health communication campaigns globally.

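### With one film per pedagogical approach, arms a, b and c compare three specific videos, so the statements about approaches and future video design should be narrowed

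*Protocol article*

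**What the plan says.** The Background and rationale section of the protocol article states that "we designed three videos, employing three research-informed pedagogical strategies": humor, analogy and emotion. The Intervention description assigns one film to each arm. Arm a "will view a video that uses a storytelling-instructional-humor approach", arm b "will view a video that uses a storytelling-analogy approach and" arm c sees the emotion-focused film. One link is given per approach (Videos A, B and C), and no approach has a second film. The same section says that "each video differs slightly in its pedagogical approach".

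The section on the choice of comparators lists what the films share: "The comparators are similar-length E-E videos, all animated in the same styles by the same animator", and "They all convey the same message (i.e., vaccines work) using a storytelling approach". It then says that contrasts among the three video groups "will allow us to explore the differential effect of these pedagogical approaches on the primary and secondary outcomes".

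The methods paragraph of the abstract also names the approaches, not the videos, as the things compared. The abstract's discussion paragraph, the end of Background and rationale and the end of the Discussion say that the results will shape later videos. The closing Discussion sentence refers to videos "using different pedagogical approaches, for improving vaccine confidence".

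Other parts are worded per video. The Objective section speaks throughout of the effectiveness of each intervention video, and Trial design describes comparing the videos with each other and with no video.

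**The concern.** The protocol moves between two targets of inference: these three films, and the pedagogical approaches behind them. The design identifies only the first. If Video A did better than Video B, the comparators section and the abstract would lead a reader to conclude that humor works better than analogy, and the future-design statements invite using that conclusion for other films. The trial would have shown only that this humor film did better than this analogy film. Recruiting 24,000 viewers does not help, because the number of films per approach stays at one.

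**Working it through.** **Structure.** There are three films and three approaches, so one film per approach. Film and approach are completely aliased in every contrast among a, b and c. With a single film per approach, variation between films of the same approach cannot be estimated from the trial's data.

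**What is held constant.** The protocol states similar length, same style, same animator, same message and no words. It mentions soundtracks but does not say whether they are shared. It does not say whether story, characters or pacing are the same.

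**The plan's own sample size** (Sample size section: difference 0.01, alpha 0.05 with divisor 2, power 80%, equal allocation):

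- SD 0.10: n = (0.10² + 0.10²) × ((1.960 + 0.842)/0.01)² ≈ 1,570 per arm. The plan states 1,570.
- SD 0.12: the same formula gives 2,261 per arm. The plan states 2,260, which agrees to rounding.

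The calculation reproduces. It covers variation between participants only, which is the right source of variation for comparing the named films.

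**Illustration of the step from film to approach.** Suppose two approaches are truly equal, but each film carries its own deviation with SD v. The protocol gives no value for v, so it is an assumption shown as a range.

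- SE of a two-arm difference = SD × √(2/n).
- SD of the observed difference = √(2v² + SE²).
- Chance of p < 0.05 = 2 × (1 − Φ(1.96 × SE / √(2v² + SE²))).

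With 12,000 per country at 1:1:1:1, n is 12,000/4 = 3,000 per arm in one country and 6,000 pooled. The SD of 0.12 is the plan's sensitivity value; the SD of 0.5 is an assumption.

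| Score SD | n per arm | SE | v = 0.001 | v = 0.005 | v = 0.01 |
|---|---|---|---|---|---|
| 0.12 | 3,000 | 0.0031 | 7.5% | 43% | 67% |
| 0.12 | 6,000 | 0.0022 | 10% | 56% | 76% |
| 0.5 | 3,000 | 0.0129 | 5.1% | 9% | 19% |

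Worked example (SD 0.12, n = 3,000, v = 0.005): SE = 0.12 × √(2/3,000) = 0.0031; √(2 × 0.005² + 0.0031²) = 0.0077; 1.96 × 0.0031/0.0077 ≈ 0.79; two-sided probability about 43%.

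The rate rises with n because a larger sample shrinks SE and leaves v unchanged. The largest v shown, 0.01, equals the difference the plan is sized to detect. The smallest gives a rate close to the nominal 5%.

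**The case against.** The formal inference is already at video level. The Objective and Trial design sections use the wording that the design supports, and the note under Secondary outcome measures speaks of differences between arms. The comparators section also grades its language: comparisons with control are to quantify, while comparisons among a, b and c are only to explore. The closing Discussion sentence has the videos, not the approaches, as its subject. All of this stands, and those video-level sections need no change.

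It does not remove the point. The abstract compares approaches without any hedge, the comparators section names the approaches as the source of the differential effect, and no section states the single-film limit. The verb *explore* does not tell a reader that film and approach are inseparable.

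Three stronger readings are tempting, and the documents do not support them:

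- A reader might infer that the films are known to differ in plot, characters, pacing and music. The protocol does not say so; these features are only not stated to be held constant.
- A reader might infer that the planned standard errors are too small. For comparing these three videos they are correct. They fall short only if each film is treated as a sample from its approach.
- A reader might take 43% to 76% as the trial's false-positive rate. Those figures rest on assumed values of v; smaller v or a larger score SD gives much lower rates.

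**Conclusion.** The point holds in a limited form. Arms a, b and c compare three specific videos. The approach-level statements in the abstract and the comparators section, and the future-design statements that draw on them, go beyond what one film per approach can show. The estimates of each video against control, the primary objective, the sample size and the tests are unaffected.

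The aliasing follows from the stated design and needs no assumption. Its numerical consequence does need one. At score SD 0.12 and 3,000 per arm, the chance of declaring equal approaches different runs from about 7.5% to 67% as the assumed between-film SD goes from 0.001 to 0.01. At score SD 0.5 it stays below 20% over the same range. These figures are illustrations of sensitivity, not estimates for this trial.

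**What to change.** Change the wording in these places:

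- **Abstract, methods paragraph, and Explanation for the choice of comparators:** describe the contrasts among a, b and c as differences between these three videos. Add that inference about the humor, analogy and emotion approaches is hypothesis-generating only, because each is represented by one film.
- **Abstract, discussion paragraph; the last paragraph of Background and rationale; the last paragraph of the Discussion:** carry the same limit into what is said about designing later videos.

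Leave the Objective and Trial design sections and the video-versus-control comparisons as they are.

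No new films, participants or analyses are needed. Separating approach from film would take several films per approach, with film as a random effect, which would be a different trial. The cost of the change is a narrower claim about pedagogy.
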